### The development of a recovery orientation in mental health in Victoria

Since the concept of recovery first emerged from the consumer movement in the 1970s and 1980s, the reorientation of mental health policy and services toward recovery has gained increasing momentum in the Victorian mental health sector [8]. At the national level, recovery was first formally endorsed in the 2003–2008 Australian National Mental Health Plan [9]. Subsequent developments in the community-managed health sector accelerated the Australian recovery movement over the following decade, including the establishment of early intervention alternatives to inpatient treatment such as the sub-acute Prevention and Recovery Care (PARC) programs. In 2011, the Victorian Government commissioned a framework document supporting the development of evidence-based recovery-oriented mental health services with an emphasis on facilitating personal recovery and dismantling barriers to full participation in community life for people with experiences of mental illness [8]. This was followed in 2014 by the implementation of a new Mental Health Act in Victoria that established recovery as a fundamental guiding principle in the provision of mental health care. Recovery has thus emerged as a core feature of contemporary reform to mental health service planning and delivery at both the state and national level. Complementing these developments has been an increasing emphasis on the importance of “co-design” or “co-production” to ensure that consumers, families and carers are centrally involved in the design, development and delivery of mental health services [10, 11]. Despite these reforms, the mental health care system still has a long way to go in being responsive to the cultural and linguistic diversity of the Australian population [12]. Little is known about the effectiveness of mental health interventions across people of different cultural and linguistic groups and whether the contemporary emphasis on recovery orientated practice is having the presumed positive impacts on consumers.

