**Fig. 1 Fig1:**
[figure not shown]
PULSAR Specialist Care study design and planned timeline Notes. Indicated at the *bottom* is the study year. The two-step cluster randomise control trial is shown: half the clusters receive the intervention in step 1 and the remaining clusters receive the intervention in step 2. For a summary of the study evaluations see Table 1

**Table 1 Tab1:** Evaluation plan for the PULSAR Specialist Care study

	Sub-study name	Evaluation design	Unit of analysis	Number	Number at each time point	Number in each cluster at each time point	Detectable differences		
							Primary outcome, QPR	Secondary outcome, WEMWBS	Secondary outcome, INSPIRE
cRCT (quantitative data)	Stream 1 (primary analysis)	cross-sectional cRCT (complete step-wedge)	Consumers (mail-out)	756	252 at baseline 252 at step 1 252 at step 2	18	6.34 (medium effect)	NA	NA
	Stream 2	pre- and post-intervention (incomplete step-wedge)	Consumers (interviews)	252 (stream 1 subset)	63 at baseline 126 at step 1 63 at step 2	9	7.68 (medium effect)	4.80 (medium effect)	7.72 (medium effect)
	Stream 3	longitudinal, (same participant, 12-mths apart pre- and post-intervention)	Consumers with diagnosis of psychosis (interviews)	88 (stream 2 subset)	44 at baseline & step 1 44 at step 1 & step 2	6–7	10.94 (medium-large effect)	6.84 (medium-large effect)	11.28 (medium-large effect)
Nested Qualitative study (qualitative data)			Consumers Staff	20–24 20–24	10–12 at step 1 10–12 at step 2	Nested sub-study examining qualitative data collected in study interviews and focus groups			
Nested Process evaluation (both quantitative & qualitative data)			Consumers & staff	The process evaluation assesses a specific set of qualitative, quantitative and documentary data relating to each cluster.					

Notes. The primary analysis examines the primary outcome– the Questionnaire about the Process of Recovery (QPR) - collected in the two-step stepped-wedge cluster randomized controlled trial (cRCT). A subset of consumers in the cRCT participate in study interviews where secondary outcomes measuring well-being, service satisfaction and health economic impact are collected In a yet another subset in the cRCT, longitudinal data are collected via interviews that are 12 months apart from consumers with a diagnosis of a psychotic disorder. Qualitative and process evaluation sub-studies are nested within the overarching cRCT and include information from consumers and staff.

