The analysis of data in a stepped-wedge cRCT is most suitably analysed in mixed-effects models [54]. The primary analysis examines the effect of PULSAR on the primary outcome (consumer-level QPR scores) using a linear mixed-effects model state ‘on an intention-to-treat basis’. The model will include intervention status and time as fixed effects and clusters and consumers as random effects. Normally step one is just to examine intervention – control group differences controlling for cluster, before including covariates. An a priori model-fitting analysis strategy will involve both univariate and multivariable models to be developed based on baseline consumer and cluster-level variables considered statistically significant (*p* < 0.10) or clinically important (e.g., age, sex), see Table 5, and included in the model as fixed. Model fit will be examined by comparing AIC values.

Secondary analyses will examine the effect of PULSAR on secondary outcomes (WEMWBS and INSPIRE) using a linear mixed-effects models to compare the intervention and control periods (pre-intervention).

Estimated intervention effects will be reported as the mean outcome difference for continuous outcomes and Odds Ratio for binary outcomes between intervention and control periods. This can be described as a meta-analysis approach as (in the case of continuous data) the mean change in each cluster will be standardized by using the variance of the outcome measure within that cluster. The estimated intervention effects will be reported with 95% Confidence Intervals and *p* values. Analysis will be conducted using Stata V.14, StataCorp. Stata Statistical Software: Release 14. College Station, TX: StataCorp LP, 2015.

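### The plan describes the reported effect in two ways that do not fit together: a time-adjusted mixed model with a raw mean difference, and a within-cluster change standardised by each cluster's own variance

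*Protocol article*

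**What the plan says.** All the relevant text is in the Protocol article, Statistical analysis, Main analysis plan for cRCT.

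- Primary model: a linear mixed model for consumer-level QPR, by intention to treat. "The model will include intervention status and time as fixed effects and clusters and consumers as random effects".
- Reported effect, first description: "Estimated intervention effects will be reported as the mean outcome difference for continuous outcomes and Odds Ratio for binary outcomes between intervention and control periods". For QPR this is a difference in points.
- Reported effect, second description, offered in the next sentence as a way of characterising the first: for continuous data, "the mean change in each cluster will be standardized by using the variance of the outcome measure within that cluster".
- Secondary outcomes (WEMWBS, INSPIRE): the analysis is described as "using a linear mixed-effects models to compare the intervention and control periods (pre-intervention", where the bracket then closes. Time is not named.

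The section then promises 95% confidence intervals and p values for the estimated effects, without saying which of the two descriptions they belong to. Sample size and Table 1 state the planning target in raw points: 6.34 for QPR in stream 1.

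**The concern.** The two descriptions are different estimators. The mixed model gives one coefficient, estimated jointly over clusters, adjusted for time and in QPR points. The second description computes a change in each cluster, rescales it by that cluster's own variability and combines the results. It has no time term and no comparison with clusters still untrained at the same date.

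That matters in this design because each cluster is observed first as control and later as intervention: "half the clusters receive the intervention in step 1 and the remaining clusters receive the intervention in step 2". A within-cluster change therefore mixes the training effect with whatever else moved over the same calendar time. The background section makes some movement conceivable, since it reports "the implementation of a new Mental Health Act in Victoria that established recovery as a fundamental guiding principle" in 2014, the year in which the clusters were randomised. The scale is also at stake: a result in units of each cluster's own variability cannot be read against 6.34 points.

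**Working it through.** **Inputs from the article.** 14 clusters, ICC 0.05, significance level 0.05 (taken as two-sided), power 0.80 (Sample size). 18 consumers per cluster per period, with "252 at baseline 252 at step 1 252 at step 2" (Table 1). Rollout: 7 clusters follow 0,1,1 and 7 follow 0,0,1 over T0, T1, T2, which are 12 months apart (Abstract, Fig. 1 caption). Sampling is cross-sectional, so a change is a change in a cluster mean between different consumers.

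**Assumed, because not given.** QPR SD of 12 to 18 points; a common linear trend of g points per year, with g = 0, 1, 2 and 4.23.

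**1. The plan's own figure.** 14 × 3 × 18 = 756, as stated. Using the Hussey–Hughes variance with period effects and total SD = 1:

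- Between-cluster variance 0.05; cluster-period error variance 0.95/18 = 0.0528.
- U = 21 (treated cells), W = 7² + 14² = 245, V = 7×4 + 7×1 = 35.
- Variance = 14 × 0.0528 × (0.0528 + 3 × 0.05) / [(14×21 − 245) × 0.0528 + (21² + 14×3×21 − 3×245 − 14×35) × 0.05] = 0.1498 / 7.486 = 0.0200.
- Detectable difference = (1.960 + 0.842) × √0.0200 = 0.396 SD.

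So 6.34 points corresponds to an SD of 6.34/0.396 = 16.0. As the SD is not stated, 6.34 can be neither confirmed nor refuted. A model without time would have a detectable difference of 0.207 SD and would need an SD of about 30.6 to give 6.34, on a scale running 0 to 88 (22 items × 4). The planning figure therefore sits more easily with the time-adjusted coefficient.

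**2. What a within-cluster change contains.** With no true effect and cluster means rising by g per year:

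- 0,1,1 clusters: (1g + 2g)/2 − 0 = 1.5g.
- 0,0,1 clusters: 2g − (0 + 1g)/2 = 1.5g.

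Both sequences carry the same amount, so averaging over clusters does not remove it. With adjacent periods only, each sequence carries 1.0g. That is also the stream 2 layout implied by 63/126/63 interviews at 9 per cluster. A trend of 1, 2 or 4.23 points per year gives a spurious 1.5, 3.0 or 6.34 points.

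**3. Effect on type I error (illustration).** Simulation with ICC 0.05, true effect 0 and 4,000 runs per setting. Each cluster's change was divided by its own SD, and the mean of the 14 was tested with a one-sample t-test. This is one reasonable version of the second description, since the article names no pooling method or test.

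| Assumed SD | g=0 | g=1 | g=2 | g=4.23 |
|---|---|---|---|---|
| 12 | 0.050 | 0.341 | 0.856 | 1.000 |
| 15 | 0.048 | 0.228 | 0.683 | 0.998 |
| 18 | 0.052 | 0.177 | 0.519 | 0.991 |

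In the same runs the time-adjusted coefficient averaged between −0.04 and 0.06 points, with rejection rates of 0.042 to 0.053 at every trend and SD.

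**4. Scale.** At SD 16, 6.34 points becomes 6.34/16 = 0.40 if divided by the SD, or 6.34/256 = 0.025 if divided by the variance as literally written. With cluster-specific divisors, the same 6.34-point change would count as 6.34/12 = 0.53 in a cluster with SD 12 and 6.34/18 = 0.35 in one with SD 18.

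**The case against.** The best defence is that the disputed sentence is only a loose gloss. It names no second model, pooling method or test. The primary model is fully specified and contains time, and the sentence just before the gloss gives a raw mean difference on the scale of the planning figure. On the natural reading, the reported effect is the model's intervention coefficient, and then none of the trend bias arises. That stands, and it means the primary model should not be criticised on this ground. It does not dispose of the point: the sentence says what will be done to each cluster's change, and that cannot be the coefficient it claims to describe.

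Three stronger readings are tempting and not supported.

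- **That a secular trend will pass into the trial's result and the randomisation is lost.** This follows only if the gloss is what is computed, and the specified model points the other way. The remark "Normally step one is just to examine intervention – control group differences controlling for cluster, before including covariates" does not name time, but as a comment on customary practice it does not take time out of that model.
- **That the secondary analyses omit time.** Their sentence is short and follows the full primary specification. Table 5 lists study month as available, and Sensitivity analyses uses time as an imputation factor for primary and secondary outcomes. In stream 2, trained and untrained clusters are both interviewed at step 1, so time can be adjusted for. The wording should be completed; it does not show that time was dropped.
- **That the documents show a marked rise in recovery scores during the trial.** They describe policy reform and give no QPR trend. A trend of zero is compatible with everything stated, and at g=0 the table shows no inflation.

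**Conclusion.** The inconsistency is real and can be seen within one section of the article, without any further document. Two descriptions of one reported effect differ in adjustment for time, in units and in how clusters are combined. The trend component of the second description (1.5g in stream 1, 1.0g for adjacent periods) follows from the rollout alone, given a common linear trend. The type I error figures rest further on the assumed SDs of 12 to 18, the assumed trends, and one chosen version of an under-described procedure, so they show what the sentence could do and do not forecast what the trial will report. If the mixed-model coefficient is what is reported, the bias is absent and only the wording is wrong.

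**What to change.** 1. Delete the sentence on the meta-analysis approach.
2. State that the reported effect for QPR, WEMWBS and INSPIRE is the intervention-status coefficient from the time-adjusted linear mixed model, in scale points, with its 95% CI and p value.
3. Name time as a fixed effect in the secondary-outcome models, as in the primary model.
4. If a standardised effect is wanted, divide that coefficient by one pooled SD and label it supplementary.

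Whether time enters as categories or continuously is a separate modelling choice and not part of this correction.

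The cost is wording only; data collection and sample size do not change. The interval is wider than for an unadjusted change. At an assumed SD of 16, the standard error is 16 × √0.0200 = 2.26 points, against 16 × √(1.5 × 0.0528/14) = 1.20 for the mean of cluster changes. The larger value is the one consistent with 6.34 at that SD, so nothing is lost against the planned power.

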#### Sensitivity analyses

A missing data analysis will investigate any patterns of missingness. For each primary and secondary outcome component with missing data, multiple imputation using multivariate regression with factors of age, gender, time, and intervention status will produce 100 estimates. Sensitivity analyses will be performed using this multiple imputation to account for missing data and then re-running the analyses. Sensitivity analyses will also include the intervention dosage variable described earlier.

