Cluster 3	Mobile support and treatment service + Community Care Unit	Monash Health	3 4	B	Mobile Support and Treatment Teams (MSTs) provide intensive long-term support through assertive outreach to people with prolonged and severe mental illness with associated high levels of disability. Community Care Units (CCUs) provide medium to long-term residential rehabilitation in a home-like environment.
Cluster 4	Mobile support and treatment service + Community Care Unit	Monash Health	5 6	B	
Cluster 5	Community Mental Health Service	Monash Health	7	C	Community Mental Health Service (CMHS) provide non-urgent assessment, treatment, case management, and continuing care support to people living in the community over varying periods of time.
Cluster 6	Community Mental Health Service	Monash Health	8	C	
Cluster 7	Continuing Care	Monash Health	9	D	Continuing Care Teams (CCTs) provide non-urgent assessment, treatment, case management, and continuing care support to people living in the community over varying periods of time.
Cluster 8	Continuing Care	Monash Health	10	D	
Cluster 9	PARC – Adult + PARC – Extended	Mind Australia	11 12	E	PARC services (including youth, adult and extended PARCs) provide short-term residential support and treatment to assist in averting acute inpatient admission or facilitate earlier discharge.
Cluster 10	PARC – Youth	Mind Australia	13	E	
Cluster 11	PARC Ermha	Ermha	14	F	
Cluster 12	PARC Ermha	Ermha	15	F	
Cluster 13	Community outreach services	Mind Australia	16	G	Community Outreach Services provide a range of individualized psychosocial support and recovery services.
Cluster 14	Community outreach services site 1 Community outreach services site 2	Ermha	17 18	G	

Note. Clusters are stratified by the team/service type and composition: i.e. there are seven different strata

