The PULSAR Specialist Care trial will take 4 years to complete, beginning in 2013 and concluding in 2017, see Fig. 1. The original study protocol (documented in the Australian New Zealand Clinical Trials Registry, or ANZCTR) was developed over a period of 18 months in consultation with Chief Investigators (CIs) and an advisory committee comprised of representatives from local specialist and community care organizations, consumers and family/carers, and experts in legal, cultural and educational aspects of mental health service delivery in Victoria. Although minor adaptations have been made to the original protocol, as outlined below, the over-arching two-step stepped-wedge cRCT design remains unchanged and the trial is on target to reach completion within the anticipated 4 year timeframe. All adaptations to the study protocol were considered by, and required the approval of, the appropriate Module Committee governing the relevant aspect of the project (see *Study leadership* section) along with the governing Human Research Ethics Committees.

The PULSAR training intervention is being delivered to 14 specialist mental health care clusters (see Table 2), with clusters randomized to receive the intervention 12 months apart, as shown in Fig. 1. To ensure that cluster types are balanced, stratified randomization was applied, for the strata see Table 2.

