Other	‘Other’ measures that are listed as 9 to 15 in Table 4 above may be investigated as independent variables when relevant. For example, the primary outcome recovery (QPR) scores may be explored for associations with the individual-level scores on the Cohesion Ladder.
Cluster level	
Cluster group	Allocated to receive the intervention at either Step 1 or Step 2.
Intervention status (0/1)	A lag time of 6 months is anticipated until intervention effects are possible. The intervention status variable indicates that this lag time has passed.
Dosage (%)	Intervention dosage.
Time since intervention	All data are time-stamped in relation to the time the intervention was received at the cluster. Time value of “0” is given for the plus/minus 3 months from date of training; “1” for 4-to-6 months post training; “2” for 7-to-9 months post training, etc. Time value of “-1” for 4-to-6 months before training; “-2” for 7-to-9 months before training, etc.
Time	Study month that survey was completed: “1” = month 1, “2” = month 2, etc.
Cluster types - stratification variables, see Table 2	
Crisis assessment & treatment team	
Mobile support and treatment service or Community Care Unit	
Community Mental Health Service	
Continuing Care team	
PARC residential facility (Mind Australia)	
PARC residential facility (Ermha)	
Community outreach service	

Consumers participating in stream 3 who report having no contact with their mental health service in the previous 12 months do not complete measures pertaining to service evaluation (CSQ, MASS, Coercion Ladder: community services version, INSPIRE).

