### Sample size

The primary analysis examines QPR data from consumers in the cRCT (stream 1) and requires a total sample size of 756 consumers from 14 clusters over 3 years (see Table 1). This will be sufficient to detect a medium effect size representing a change in QPR score by 6.34, see Table 1. Secondary analyses that examine data from a subset of stream 1 consumers who participate in stream 2 of the cRCT, requires a total sample size of 252 consumers over the study period. This will be sufficient to detect medium effect sizes in the QPR and two secondary outcome measures (WEMWBS and INSPIRE), see Table 1. Additional secondary analyses to examine longitudinal data from a subset of stream 2 consumers who participate in stream 3 of the cRCT, requires a total sample size of 88 consumers over the study period. This will be sufficient to detect medium-large effect sizes in the QPR and WEMWBS and INSPIRE, see Table 1.

Sample size calculations were based on 14 clusters; intracluster correlation coefficient (ICC) of 0.05; significance level set at 0.05; power of 0.80; and available published [34, 36, 45] and unpublished (INSPIRE) data about distribution properties. All sample size calculations indicate the minimum number of participants we aim to recruit and were done using Stata statistical software *stepped-wedge* [46] Version 11, StataCorp. 2009.

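### The seven randomisation strata are only candidate covariates, and the sensitivity imputation omits cluster and stratum; both should be pre-specified, at modest gain

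*Protocol article*

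**What the plan says.** Design. The Overall design section states: "To ensure that cluster types are balanced, stratified randomization was applied, for the strata see Table 2". The note to Table 2 confirms the number: "Clusters are stratified by the team/service type and composition: i.e. there are seven different strata". Each stratum holds two clusters, and the Allocation section describes one randomisation key per stratum.

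Primary model. The Main analysis plan for the cRCT states: "The model will include intervention status and time as fixed effects and clusters and consumers as random effects". Further consumer-level and cluster-level covariates from Table 5 are added if they reach p<0.10 or are considered clinically important; age and sex are the examples given. Table 5 lists the cluster types, labelled as the stratification variables, among these candidates.

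Missing data. The Sensitivity analyses section applies, to each primary and secondary outcome component with missing values, "multiple imputation using multivariate regression with factors of age, gender, time, and intervention status will produce 100 estimates", and then repeats the analyses on the imputed data. Cluster and stratum are not in the list.

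A measure withheld by design. Below Table 5, the article says that "Consumers participating in stream 3 who report having no contact with their mental health service in the previous 12 months" do not complete the service-evaluation measures. INSPIRE is one of these, and it is also a secondary outcome.

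**The concern.** A factor used to restrict the randomisation belongs in the analysis because of the design, not because it passes a test in the data. The strata here run from crisis teams to long-term residential and outreach services, so they may carry a good part of the differences between clusters. If they stay out of the model, that part remains in the cluster variance and the interval is wider than the design allows. If they enter through a screen, the form of the primary model depends on the data, and with seven pairs of clusters the screen has little power.

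The imputation raises a separate issue. Values drawn without a cluster term carry no cluster effect, yet the completed data go into a model that estimates one. The two models are uncongenial: between-cluster variance is diluted, and the standard error can be affected. In stream 3, the first-interview score is likely to be a strong predictor of a missing second score, and it is not in the stated list. Read literally, the rule would also impute ratings of worker support for people who had no service contact to rate.

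**Working it through.** **Inputs.** From the Sample size section: "Sample size calculations were based on 14 clusters; intracluster correlation coefficient (ICC) of 0.05; significance level set at 0.05; power of 0.80"; "requires a total sample size of 756 consumers from 14 clusters over 3 years"; "This will be sufficient to detect a medium effect size representing a change in QPR score by 6.34". From Table 1: 18 per cluster per time point, and 14 × 18 × 3 = 756. Two-sided testing is assumed. The article gives no SD.

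**Reproducing 6.34.** In the stepped-wedge cluster-mean formula, with total variance 1, let s = 0.95/18 = 0.0528 and τ² = 0.05, with I = 14 clusters and T = 3 periods. Seven clusters follow the pattern 0,1,1 and seven 0,0,1, so U = 21, W = 245 and V = 35.

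Var = I·s·(s + Tτ²) / [(IU − W)s + (U² + ITU − TW − IV)τ²] = 14 × 0.0528 × 0.2028 / (49 × 0.0528 + 98 × 0.05) = 0.0200

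SE = 0.1415, and the detectable difference is (1.960 + 0.842) × 0.1415 = 0.396 SD. Then 6.34/0.396 = 16.0. An SD of 16 fits the stated figure but is back-calculated, so this does not independently confirm 6.34.

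**Strata as fixed effects, stream 1.** Each stratum has one cluster in each sequence, so stratum terms simply reduce τ² by the share they explain. The share is assumed, and degrees of freedom are not deducted.

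| Share of τ² explained | τ² left | SE ratio | Detectable difference | Power at 6.34 |
|---|---|---|---|---|
| 0% | 0.0500 | 1.000 | 6.34 | 80.0% |
| 25% | 0.0375 | 0.987 | 6.26 | 81.0% |
| 50% | 0.0250 | 0.968 | 6.14 | 82.5% |
| 80% | 0.0100 | 0.926 | 5.87 | 85.7% |

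The gain is 1-7%. It is modest because the random cluster effect already lets the model use within-cluster contrasts.

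**Stream 2.** Each half of the clusters is observed in only two periods, 9 per cluster each time. With period effects fitted, the T0 and T2 data each come from one half only, so the effect rests on the T1 contrast of 7 against 7 clusters: Var = 2(τ² + 0.95/9)/7. At SD 16 the detectable difference is 9.45 with no strata, and 9.06, 8.66 and 8.14 at shares of 25%, 50% and 80%. This 9.45 baseline is a recalculation; Table 1 prints 7.68. The cost of the 6 df, comparing t(0.975) + t(0.80) on 7 and 12 df, is 3.26/3.05 = 1.07. A strict count of 12 − 6 = 6 df gives 3.35/3.05 = 1.10. After the factor 1.07, the three figures become 9.68, 9.25 and 8.70. The net result against 9.45 is a small loss at 25%, about a 2% gain at 50% and about 8% at 80%. At 1.10, the 50% gain also disappears (9.51).

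**Power of the p<0.10 screen.** Take a between-strata F test of cluster means on 6 and 7 df, with 54 consumers per cluster, error 0.95/54 = 0.0176 and critical value 2.83. The expected mean-square ratio is 1.45, 2.17 and 3.90 at shares of 25%, 50% and 80%. The chance that the strata pass is about 20%, 37% and 64%.

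**Imputation without cluster.** If a fraction m is missing and imputed with no cluster effect, a cluster's mean keeps only (1 − m) of its own effect. The ICC therefore falls to about (1 − m)² × 0.05: 0.041 at 10% missing, 0.032 at 20% and 0.0245 at 30%. Simulation of the stream 1 layout (200 trials, 10 imputations, imputing on time and intervention status) gave:

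| Missing (assumed) | ICC, complete data | ICC, no cluster in imputation | Model SE, without v with cluster | Empirical SE, without cluster | Coverage, without cluster |
|---|---|---|---|---|---|
| 10%, uniform | 0.047 | 0.038 | 0.147 v 0.148 | 0.146 | 94.0% |
| 30%, uniform | 0.049 | 0.024 | 0.165 v 0.171 | 0.158 | 96.5% |
| 30%, varying by cluster-period | 0.047 | 0.025 | 0.164 v 0.174 | 0.176 | 92.5% |

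Bias was negligible throughout. In the last row the model SE is 0.164/0.176 = 0.93 of the empirical SE, about 7% too small; in the other two rows it is not too small. With 200 trials, an empirical SE carries about 5% simulation error and a coverage figure about 1.5 points. Imputing with fixed cluster indicators overshot the ICC (0.064 at 30% missing), which favours a multilevel imputation model.

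**The case against.** A reader might infer that the analyses ignore the clustered design. The documents do not support that: clusters are a random effect in the primary model, the imputed data go back through the same analyses, and the ICC is to be reported. Nor is the p<0.10 rule the only route in. The clinical-importance route is open, since age and sex are only examples, and the strata could enter that way. What stands is that their entry is not guaranteed.

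The share of variance due to strata is not in the article, and the stream 1 gain is small across the range shown. A claim of a clear precision gain in stream 2 does not survive, because the degrees of freedom absorb much or all of it.

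The missing rates are also assumed, and 20-30% is hard to defend for stream 1. That stream is a cross-sectional mail-out; people who do not reply leave no record to impute, so missing values are mainly skipped items on returned forms. High rates are more plausible at the stream 3 follow-up, given the 26% attrition that the Background reports for the UK predecessor trial. The harm is in any case confined to a sensitivity analysis.

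Finally, the article does not say that a measure withheld by design counts as missing, and such handling could be settled in a fuller document. This is fair, but the rule as printed covers every secondary outcome with missing data, and INSPIRE is one. It does not reach the satisfaction surveys or the Coercion Ladder, which are listed as other measures.

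**Conclusion.** The point holds as a cheap improvement to two stated rules, not as a flaw that biases the trial. A randomisation factor should not depend on a screen that it would pass with a probability of about 20-64% over the assumed range. Committing to the strata lowers the stream 1 detectable difference from 6.34 to 6.26-5.87, on an ICC of 0.05, a back-calculated SD of 16 and an assumed share of 25-80%. In stream 2 the net effect lies between a small loss and a modest gain.

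The imputation list is uncongenial with the model it feeds. The imputed re-run would show an ICC of about 0.025 instead of 0.05 at an assumed 30% missing, and about 0.04 at 10%. A reader might infer that this also costs precision or distorts the effect; the simulations show an unbiased effect, coverage of 92.5-96.5% and no consistent loss of precision. Standard errors can be slightly too small, about 7% in the worst case run.

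**What to change.** 1. State that the seven strata enter the primary model as fixed effects whatever their p value, and take them out of the Table 5 candidate list. If they are left out because there are only 14 clusters, give that reason in advance.
2. Replace the imputation model with a multilevel one that includes cluster and stratum as well as age, gender, time and intervention status. For stream 3, add the first-interview score.
3. State that INSPIRE is not imputed for stream 3 participants to whom it was not given because they had no service contact, and define the analysis set for INSPIRE accordingly.

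Cost: slightly more analysis code and no new data. The strata use 6 degrees of freedom. This matters mainly in stream 2, where it widens intervals by about 7-10% before any gain, so if the strata are carried into the stream 2 models, that should be decided in advance with this cost in view.
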